##### Relevant concomitant care permitted or prohibited during the trial {11d}

Women who participated in this trial cannot participate in another trial.

#### Provisions for post-trial care {30}

Not applicable as no adverse event will be related to the trial due to the absence of any medication.

### Outcomes {12}

#### Primary outcome

The primary outcome will be the prevalence of FGR at birth, defined as newborns with a BW below the 10th centile [43] according to local standards [44].

#### Secondary outcomes

The following are the secondary outcomes:
(i)APO is defined as any of the following outcomes: (a) preterm birth, delivery <37 weeks’ gestation; (b) preeclampsia, defined as systolic blood pressure (SBP) ≥ 140 mmHg or diastolic blood pressure (DBP) ≥ 90mmHg at least 4 h apart after 20 weeks of gestation and proteinuria of ≥300 mg in 24 h; (c) perinatal mortality, fetal or neonatal mortality (within 28 days of life); (d) severe FGR, BW <3rd centile; (e) metabolic acidosis, an umbilical artery pH below 7.10 and/or base excess >12 mEq/L in the new-born and/or an Apgar score at 5 min below 7.0 assigned by the attending neonatologist or midwife; and (f) major neonatal morbidity in the presence of any of the following: intraventricular hemorrhage grade III/IV, necrotizing enterocolitis, periventricular leukomalacia, sepsis, bronchopulmonary dysplasia, and hypoxic-ischemic encephalopathy.(ii)Bayley-III score at 2 years of corrected postnatal age will be evaluated by means of their four items score (raw and scaled): (a) cognitive, (b) language, (c) motor, and (d) socio-emotional.(iii)The cardiovascular system at 2 years of corrected postnatal age will be evaluated by (a) SBP, (b) DBP, (c) mean arterial pressure, and (d) heart rate.

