#### Intervention description {11a}

##### Nutrition program based on MedDiet

The dietary intervention is adapted from the PREDIMED (*Prevención con Dieta Mediterránea)* trial [18]. The main goal of the intervention strategy is to change general dietary patterns rather than focusing on changes in single food or macronutrients. The diet pattern will be adapted to pregnant women in general and will be further adapted after the first individual assessment visit with the dietician, according to the participant’s weight and culture. The intervention will be performed in individual 30-min visits plus a 1-h group session every month. Participants will also be provided with extra-virgin olive oil (2 l every month) and 15 g of walnuts per day (450 g every month) at no cost. Every 2 weeks, the woman will receive a phone call from the dietician in order to reinforce the intervention. Specific materials (recipes, a quantitative 1-week shopping list of food items according to the season of the year, a weekly plan of meals with detailed menus) will be given in each visit and will also be available in the Nutrition section (login with a password given at the moment of randomization) on the trial website (https://fetalmedbarcelona.org/impactbcn/). During each monthly visit, the 17-item dietary screener to assess baseline adherence to the MedDiet will be checked, and a 3-day dietary register will also be evaluated. In addition, blood pressure and weight gained will be measured.

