### Sample size {14}

The study sample size (*n*=1218; 406 per arm) has been calculated assuming a type I error of 5% and aiming for a power of 80% for the most restrictive endpoint (reduction of 50% of the rate of APO). The sample size required for that secondary endpoint was actually more restrictive than the one required for the primary endpoint (reduction of 30% of the rate of neonates born with a BW <10th centile, *n*=1101; 367 per arm).

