### Assignment of interventions: allocation

#### Sequence generation {16a}

The computer-generated randomization sequence is based on restricted randomization, with a forced strict number of participants per branch at the end of the trial. It is protected and managed by a computer technician of the foundation “*Medicina Fetal Barcelona*” which has no role in recruitment. The investigators enter data of the patient that is recruited on a website, and the computer generates automatically the inclusion number and treatment assignment. Participants are randomly assigned to either usual care, MedDiet, or MBSR with a 1:1:1 allocation as per computerized random number generator, with equal proportion in each group. An additional code is also generated, so the patient can have access to the official website of the study to a specific part according to her intervention (https://fetalmedbarcelona.org/impactbcn/).

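### The metabolic-acidosis component of APO, the composite that fixed the sample size, has the wrong sign on base excess; as a smaller point, scheduled maternal blood-pressure checks are described for the MedDiet arm only

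*Protocol article*

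**What the plan says.** **Acidosis.** In the Protocol article, Secondary outcomes, APO is met by any one of six components. Component (e), labelled metabolic acidosis, is "an umbilical artery pH below 7.10 and/or base excess >12 mEq/L in the new-born", joined by a further and/or to a 5-minute Apgar score below 7. Any one of the three limbs is therefore enough. No other section restates the base-excess limit.

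**Role of APO.** Sample size {14} arrives at 406 per arm "assuming a type I error of 5% and aiming for a power of 80% for the most restrictive endpoint", namely a "reduction of 50% of the rate of APO". It adds: "The sample size required for that secondary endpoint was actually more restrictive than the one required for the primary endpoint". The primary outcome needed 367 per arm.

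**Preeclampsia.** Component (b) needs raised pressure on readings separated by at least 4 hours and also at least 300 mg of protein in a 24-hour urine. Under Nutrition program based on MedDiet, the monthly dietitian visit carries this addition: "In addition, blood pressure and weight gained will be measured". The MBSR description, Table 1 and the data-collection section {18a} describe no matching maternal measurement in the other arms. Section {23} provides for review of endpoint records by staff masked to group.

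**The concern.** Metabolic acidosis is a deficit of base, which is a negative base excess. A limit written as greater than +12 selects the opposite disturbance. Because that limb can make a case alone, the slip is not harmless if it is programmed from the text: a signed laboratory value tested against >12 would pass over the intended newborns. The affected endpoint is the one to which the trial's size was fitted, so lost or spurious events would cost power on that comparison.

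The second issue is detection. The trial is open-label, and one arm has a described schedule of extra blood-pressure readings. A high reading can lead to repeat measurement and a urine test, so true preeclampsia may be picked up somewhat more often in that arm.

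**Working it through.** **1. What the rule does as written.** Take newborns with pH at or above 7.10, Apgar at or above 7, and no other APO component:

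| Base excess (mEq/L) | Intended rule (< −12) | Written rule (> 12) |
|---|---|---|
| −14 | event | no event |
| 0 | no event | no event |
| +13 | no event | event |

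A newborn with base excess −14 and pH 7.05 counts under both rules through the pH limb. The net loss to APO is therefore confined to newborns who qualify by base deficit and by nothing else in the composite. The document gives no rate for that group.

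**2. The plan's sample size.** Inputs from Sample size {14}: 406 per arm, 50% relative reduction, 80% power, alpha 5%. Two-sidedness is taken from section {20b}, which tests secondary endpoints at 0.05 two-sided. The control APO rate is not stated, so 406 cannot be reproduced directly and the rate has to be back-solved.

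n per arm = [1.960·√(2p̄q̄) + 0.842·√(p₁q₁ + p₂q₂)]² / (p₁ − p₂)²

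With p₁ = 0.1065, p₂ = 0.05325 and p̄ = 0.0799: (0.7514 + 0.3211)² / 0.05325² = 1.1504 / 0.002836 = 405.7, so 406. The implied reduction is about 10.65% to 5.3%. The same formula gives 367 for 30% versus 21%, which matches the primary-outcome figure (the 30% is also back-solved). Varying alpha, sidedness, continuity correction and dropout (0 to 15%), the implied control APO rate runs from 8.35% to 16.15%. The 10.65% is therefore a working assumption.

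**3. Illustration: events missed equally in all arms.** Multiply both rates by (1 − m), where m is an assumed share of true APO events lost.

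Power = Φ{[(p₁ − p₂)√n − 1.960·√(2p̄q̄)] / √(p₁q₁ + p₂q₂)}

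For m = 10%: p₁ = 0.09585, p₂ = 0.04793, so (0.9657 − 0.7160) / 0.3637 = 0.687 and power is 75.4%.

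| Share lost (assumed) | Power at 406 per arm | n per arm for 80% |
|---|---|---|
| 0 | 80.0% | 406 |
| 5% | 77.8% | 429 |
| 10% | 75.4% | 455 |
| 20% | 70.0% | 517 |

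The loss in power is similar at other control rates. At 8.7% it goes from 70.9% to 68.6, 66.1 and 60.6%; at 12% from 84.9% to 82.9, 80.6 and 75.5%.

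**4. Illustration: false events in all arms.** If 0.5, 1 or 2% of non-events were wrongly counted, power would be 77.6, 75.2 or 70.5%. These shares are assumed too.

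**5. Illustration: extra preeclampsia detection in MedDiet.** Monthly visits over weeks 24 to 36 (Table 1) give about 3 to 4 extra readings. As one assumed case, preeclampsia at 5% with detection of 95% against 85% adds 5% × 0.10 = 0.5 percentage points.

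| Points added to MedDiet APO (assumed) | Observed risk ratio | Power, MedDiet vs control |
|---|---|---|
| 0.5 | (5.325 + 0.5)/10.65 = 0.55 | 70.6% |
| 1 | 0.59 | 59.9% |
| 2 | 0.69 | 38.1% |

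These are upper values for each detection gap, because they treat every extra detected case as a new APO event. Some such women would already count through preterm birth or severe FGR.

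**The case against.** **On the sign.** The component is labelled metabolic acidosis and sits beside a low pH and a low Apgar score, so base deficit above 12 is very probably what was meant. A reader might infer that events in this trial are in fact misclassified and that power has been lost. The document does not show that: nothing indicates how the variable is coded, the pH and Apgar limbs still work, and no component rate is given. What stands is that the published threshold is wrong, can make a case by itself, and is corrected nowhere else in the article.

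**On blood pressure.** A reader might infer that pressure is measured in one arm only. That goes beyond the text. Women in every arm are high-risk pregnancies at a referral centre, and a condensed article need not list routine antenatal checks. A dietitian's reading cannot make a case without a repeat and proteinuria. Masked record review also limits differential classification, although it cannot equalise how often pressure was taken. The detection gaps above are assumptions. What stands is an asymmetry in the measurements the protocol describes.

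**On consequence.** APO is a secondary endpoint tested without alpha adjustment, for an exploratory purpose. Extra detection would work against MedDiet, so it cannot manufacture a benefit, and it leaves MBSR versus control untouched.

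**Conclusion.** The sign error is definite and should be corrected, because it sits in a component of the endpoint that determined N = 1218. It is non-differential between arms, and its effect cannot be sized from the document. The power figures show only what given losses would cost, assuming a control APO rate near 10.65%. They are not estimates of what has happened. The primary outcome, birth weight below the 10th centile, is unaffected by either issue.

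The blood-pressure issue is secondary and smaller. It rests on the absence of a described counterpart in the other two arms, works only by prompting a work-up, and would bias against MedDiet alone. It justifies a cheap check and does not support a claim that the MedDiet result is invalid.

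**What to change.** 1. In Secondary outcomes, component (e), write base deficit >12 mEq/L (base excess < −12 mEq/L), and code it that way in all arms. Before programming, confirm whether the laboratory exports a signed base excess or an unsigned deficit. Cost: one line and no new data.
2. State that preeclampsia is classified from records common to all arms, by the masked review already planned, without using dietitian-visit readings. Cost: one sentence; those readings are set aside for this endpoint.
3. Add a sensitivity analysis of APO without the preeclampsia component. Cost: one extra table row.

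Items 2 and 3 reduce unequal detection but do not remove it: a high dietitian reading can still prompt a work-up that enters the hospital record, and that woman may then reach another component.

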### Participant timeline {13}

Figure 1 shows the flow chart of participants, and Table 1 shows the study timeline.

**Fig. 1 Fig1:**
[figure not shown]
Flow chart of participants in the randomized controlled trial. FGR, fetal growth restriction; RCOG, Royal College of Obstetrics and Gynaecologists; MBSR, mindfulness-based stress reduction; APO, adverse perinatal outcome; PE, preeclampsia

**Table 1 Tab1:** Study timeline

	Enrolment	Allocation	Post-allocation								Close-up
***Time point***	***Pregnancy***	***Pregnancy***	***Pregnancy***				***Delivery***	***Postpartum***			***Postpartum***
	*19–23.6 weeks*	*19–23.6 weeks*	*21–24.6 weeks*	*24–36 weeks*	*34–36.6 weeks*	*36–38 weeks*		*1–3 months*	*12 months*	*24 months*	*24 months*
	Screening visit	Randomization visit	Initial visit	Interventions	Final visit	Extra visit		Postnatal follow-up			
**Enrollment:**											
Eligibility screen	√										
Informed consent		√									
Allocation		√									
**Interventions:**											
MD				√							
MBSR program				√							
Usual care				√							
**Assessments:**											
Baseline variables											
Sociodemographic data			√								
Medical history			√		√						
Maternal life-style assessment			√		√			√		√	
Maternal nutritional assessment			√		√						
Outcome variables											
Primary outcome							√				
Perinatal outcomes							√	√			
Infant Bayley-III										√	√
Infant cardiovascular assessment										√	√
Other variables											
*Biological samples:*											
Maternal biological samples			√		√			√		√	
Feto-placental biological samples							√				
Infant biological samples								√		√	
*Maternal and fetal imaging:*											
Feto-placental US assessment					√						
EFW and feto-placental Doppler					√						
Fetal echocardiography					√						
Fetal neurosonography					√						
Maternal and fetal magnetic resonance rimaging						√					
*Infant extra tests:*											
Infant NBAS								√			
Infant ASQ									√		

*MedDiet* Mediterranean diet, *MBSR* mindfulness-based stress reduction, *US* ultrasound, *EFW* estimated fetal weight, *NBAS* Neonatal Behavioral Assessment Scale, *ASQ* Ages and Stages Questionnaires

### Sample size {14}

The study sample size (*n*=1218; 406 per arm) has been calculated assuming a type I error of 5% and aiming for a power of 80% for the most restrictive endpoint (reduction of 50% of the rate of APO). The sample size required for that secondary endpoint was actually more restrictive than the one required for the primary endpoint (reduction of 30% of the rate of neonates born with a BW <10th centile, *n*=1101; 367 per arm).

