### Eligibility criteria {10}

Eligible participants will be pregnant women at high risk to develop FGR during pregnancy according to the criteria of the Royal College of Obstetricians and Gynaecologists (RCOG) (odds ratio (OR) >2) [38].

The inclusion criteria are as follows:
Age ≥18 yearsSpeaking Spanish fluentlyLive singleton non-malformed fetusHigh-risk pregnancy to develop FGR (meeting the criteria of the RCOG)19.0–23.0 weeks of gestation

The exclusion criteria are as follows:
Fetal anomalies including chromosomal abnormalities or structural malformations detected by ultrasound prenatally and congenital infectionsNeonatal abnormalities diagnosed after birthMental retardation or other mental or psychiatric disorders that impose doubts regarding the true patient’s willingness to participate in the studyNo possibility to come to additional visitsIncluded in other RCT studies

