### Statistical methods

#### Statistical methods for primary and secondary outcomes {20a}

The statistical analysis will follow the general regulatory recommendations given in the ICHE9 Clinical Trials guidelines [53].

The inferential analysis for the main variable (proportion of newborns with a BW below the 10th centile) will be performed by means of OR using a logistic regression model, with a 95% IC. The method of Hochberg will be used for the adjusted *p* values for the comparison of each interventional arm vs. control, i.e., the result *p* values of two comparisons will be ordered descending; the following decisions about the positive results of the study will be considered:
If the highest *p* value will be lowest than the threshold (0.0490), the study is positive for the two interventional arms vs. control.If the highest *p* value will be higher than the threshold (0.0490), the study is not positive for this, and the next variable *p* value should be lowest than the 0.0245 (0.0490/2) to be able to conclude the positive comparison of this interventional arm vs. control.

The specific analysis will be as follows:
Modified intention-to-treat population (mITT), defined as all randomized patients with neonates who did not end with a congenital malformation, diagnosed during pregnancy or in the postnatal period.Population per-protocol (PP), defined as all subjects included in mITT that participated in at least one visit without protocol deviation that might impact the study’s main assessments. The protocol deviation considered in this study is the low compliance with treatments. The next compliance criteria will be a reason for exclusion:
MBSR group: the patient attends less than 6 of 9 sessions (<67%).Nutrition group: the patient has a MedDiet score at final assessment <3 from the initial score.

The patient who withdrew informed consent will be excluded from all populations.

The main study analysis will be performed using the mITT, pre-randomization and baseline analyses, and primary and secondary efficacy analyses. The primary outcome analysis will also be performed using also ITT population as a supportive, PP population to test the robustness of the results.

No inferential analysis will be performed for the baseline comparability.

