### Methods for additional analyses (e.g., subgroup analyses) {20b}

For the secondary analyses, no alpha adjusted will be made; all secondary statistical tests will be applied with a 0.05 two-sided significance level due to the exploratory purpose. All details are explained in the statistical analysis plan.

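### The primary sample size (367 per arm for 80% power) uses a 5% error and ignores the 0.0245 Hochberg step; if only one intervention works, 406 per arm gives about 76%

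*Protocol article*

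**What the plan says.** Protocol article, Sample size {14}: the size "has been calculated assuming a type I error of 5% and aiming for a power of 80% for the most restrictive endpoint". That endpoint is the adverse perinatal outcome (APO) composite, with a target "reduction of 50% of the rate of APO", giving 406 per arm and 1218 in total. The primary endpoint is said to need fewer: "reduction of 30% of the rate of neonates born with a BW <10th centile, *n*=1101; 367 per arm". The section gives no control rate for either endpoint, does not say whether the 5% is one- or two-sided, and mentions no division of alpha between the two comparisons with usual care.

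Statistical methods for primary and secondary outcomes {20a}: the two primary comparisons are tested by Hochberg. If the larger p value is below 0.0490, both interventions are positive. If not, the smaller one "should be lowest than the 0.0245 (0.0490/2) to be able to conclude the positive comparison".

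Interim analyses {21b}: the final level of 0.0490 is two-sided.

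Methods for additional analyses {20b}: secondary endpoints, which include APO, are not adjusted; "all secondary statistical tests will be applied with a 0.05 two-sided significance level due to the exploratory purpose".

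**The concern.** The sample size and the primary test rest on different error levels. The size is stated at 5%. An intervention that works while the other does not will usually be judged at 0.0245, about half that. A size that gives 80% power at 5% gives less at 0.0245.

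The case of one effective intervention is realistic. Diet and mindfulness training have separate rationales in the Introduction, and each is compared separately with usual care. A reader of the Sample size section would conclude that 1101 women give 80% power for each intervention on fetal growth restriction, and that 1218 give more than that. If the power for a single effective arm is in fact below 80%, a non-significant result for one intervention is likely to be read as stronger evidence of no effect than it is.

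**Working it through.** **Inputs.** From the protocol article: 30% relative reduction in the primary endpoint, 80% power, 5% error, 367 and 406 per arm, 1:1:1 allocation, Hochberg thresholds 0.0490 and 0.0245 (two-sided). Assumed, because not stated: the control rate.

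**Formula.** Two proportions, pooled variance under the null, no continuity correction:

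n per arm = [z_α √(2 p̄(1−p̄)) + z_β √(p₁(1−p₁) + p₂(1−p₂))]² / (p₁−p₂)²

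**Step 1: reproduce 367.** Take p₁ = 0.30 and p₂ = 0.7 × 0.30 = 0.21, so p̄ = 0.255. The two square roots are 0.6164 and 0.6131, and the difference is 0.09.
- Two-sided 0.05 (z_α = 1.960, z_β = 0.842): n = (1.2081 + 0.5160)² / 0.0081 = 366.99, so 367. This matches the plan with no allowance for losses.

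**Step 2: the level an arm must reach alone.**
- Two-sided 0.0245 (z_α = 2.249): n = (1.3864 + 0.5160)² / 0.0081 = 446.8, so 447 per arm; 3 × 447 = 1341.

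**Step 3: power at fixed thresholds.** Power = Φ{[0.09 √n − z_α × 0.6164] / 0.6131}.

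| n per arm | at 0.05 | at 0.0490 | at 0.0245 |
|---|---|---|---|
| 406 | 83.8% | 83.6% | 75.7% |
| 367 | 80% | – | 70.9% |

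**Step 4: the full Hochberg rule.** Simulation with a shared control arm, 30% in control and 21% in an effective arm, final analysis only, 400,000 replicates:

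| n per arm | One works: power for that arm | Both work: each arm | at least one | both |
|---|---|---|---|---|
| 367 | 71.3% | 77.3% | 86.1% | 68.7% |
| 406 | 76.2% | 81.7% | 89.4% | 73.9% |
| 447 | 80.5% | 85.4% | 92.0% | 78.8% |

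**Step 5: sensitivity to the unstated control rate.**
- Two-sided 5% with 0 to 20% losses built in: control rates of about 30% to 35% reproduce 367 to within one. Each gives 446 to 447 per arm at 0.0245 and about 76% power at 406. The reason is that (z_α + z_β)² rises by a factor of 1.217 whatever the rate, and 367 × 1.217 ≈ 447.
- One-sided 5%: 25% against 17.5% also gives 367. The 0.0245 level then needs 568 per arm, and 406 gives 64%.
- Alpha already split to two-sided 0.025: 367 needs a control rate near 34.5%. The 0.0245 level then needs 369, and 406 gives 84%. Only this reading removes the shortfall.

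**Step 6: which endpoint needs more women.** At two-sided 0.05, a halving of APO needs 406 per arm if the control rate is about 10.65% (also back-solved).

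| Alpha | Primary | APO |
|---|---|---|
| 0.05 for both | 367 | 406 |
| 0.0245 for both | 447 | about 494 |
| as the plan tests (primary arm alone 0.0245, APO 0.05) | 447 | 406 |

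**The case against.** The strongest reply is that the shortfall is conditional and modest. Hochberg's first threshold is 0.0490, and if both interventions achieve the 30% reduction, 406 per arm keeps about 82% power for each. Only one scenario falls below 80%, by about four percentage points. This stands, and it is why no increase in the sample size is asked for.

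The second reply is that the control rate is back-solved, so matching 367 proves little: it fits one free parameter. This stands in part. A split alpha with a rate near 34.5% fits equally well. But the section states 5% and mentions no split, and the unadjusted reading gives the same 447 and 76% across a range of rates and losses.

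The third concerns the ranking of endpoints. A reader might infer that calling APO the most restrictive endpoint is an arithmetic error. It is not: at any common alpha checked, APO needs more women. The order reverses only at the unequal levels that the plan actually applies.

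**Conclusion.** The claim that 1101 women give 80% power for the primary endpoint is wrong as written for a single effective intervention. Assuming 30% against 21%, that size gives about 71% in that case, and the planned 406 per arm gives about 76%. If both interventions work, 406 per arm gives about 82% each. These figures assume complete outcomes, a 5% sizing level that was two-sided and not split, and no contribution from the interim look.

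Four stronger readings are tempting but not supported:

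- **The two implied control rates contradict each other**, because APO contains birth weight below the 3rd centile. A normal shift would put about 13% below the 3rd centile when 30% are below the 10th, more than the implied 10.65% for all of APO. Keeping the 3:10 ratio gives 9%, which fits. Both rates are back-solved and neither model is in the document.
- **The true control rate is nearer 18%**, from doubling the odds on 10%. The eligibility figure "odds ratio (OR) >2" is a minimum for a risk factor, and the 7–10% in the Introduction refers to all pregnancies, not to an unexposed group.
- **No losses were allowed for.** A back-solved rate cannot show this: higher rates with losses give the same 367.
- **APO must be formally gated because it set the size.** The plan openly labels secondary tests exploratory, and sizing on a demanding secondary endpoint is permissible. Holding APO to 0.0245 would cut its power at 406 per arm to about 71% before any gating.

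**What to change.** Keep 1218 and amend the Sample size section:

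1. State the control rate assumed for each endpoint, the sidedness of the 5%, and whether alpha was split between the two comparisons.
2. Replace the claim that 1101 gives 80% power for the primary endpoint with the power of 406 per arm under the Hochberg thresholds. If the assumption was 30% against 21%: about 76% if one intervention works; about 82% per arm, 89% for at least one and 74% for both if both work. If another rate was used, recompute these figures.
3. Qualify the statement that APO is the most restrictive endpoint: it holds when both endpoints are judged at the same alpha. At the levels the plan uses, 0.0245 for one primary arm and 0.05 for APO, the primary needs more.

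The cost is a slightly less favourable stated power. No participant, test or threshold changes.
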